### Design and setting

This study is a multicenter randomized controlled study with two treatment conditions: treatment as usual (TAU) and motivation feedback (additional to TAU). There will be two extensive measurement occasions for both groups: at baseline and follow-up at 12 months.

Twelve departments within the Mental Health Center West North Brabant (MHC WNB), and the Mental Health Center BreBurg (MHC Breburg) located in the south west of the Netherlands, were approached to participate in the study. The MHC WNB and MHC Breburg provide mental health care to varying patient populations, including patients with a primary diagnosis of psychotic and/or personality disorder who will be targeted for this study. The current study will take place at several treatment locations of the MHC WNB and MHC Breburg, and represents a partnership between these centers and the Epidemiological and Social Psychiatric Research institute (a research center within the Erasmus Medical Center in Rotterdam, the Netherlands).

### Study population: inclusion and exclusion criteria

The current study aimed for patients with severe mental illness treated in outpatient community mental health care, and although there are several definitions of severe mental illness, most definitions include a diagnosis of severe psychiatric disorder, a treatment duration or illness duration of at least two years and several disabilities [34,35]. Since patients with psychotic disorders constitute the majority of patients treated in assertive community mental health teams in the Netherlands [33,36] and patients with severe personality disorders constitute another significant part of the caseload, combined with clinical observations that these two diagnostic groups may especially benefit from interventions aimed at improving treatment motivation and treatment engagement, it was decided to incorporate both patient groups into the study.

The research participants will consist of patients with a primary diagnosis of a psychotic disorder and/or a personality disorder, and their clinicians. Patients are eligible for participation if they are aged between 18 and 65 years old and receive individual outpatient treatment for their psychotic and/or personality disorder. Exclusion criteria are insufficient command of the Dutch language and/or a documented diagnosis of organic psychosyndrome (e.g. dementia or chronic toxic encephalopathy).

Clinicians will be eligible for participation if they are the primary health care practitioner involved with the patient, meaning that he/she is the one that has the most frequent contacts with this patient. It is expected that the resulting group of clinicians will mainly consist of specialized social workers, specialized psychiatric nurses and psychologists with relevant treatment experience with this patient population.

### Methods

In order to test the three motivational theories while also trying to limit the level of response burden for study participants in our intervention trial, proper choices for instruments had to be made. To ensure that we measure constructs appropriately for each theory, we tried to stay as close as possible to the original measures used by Ryan and Deci [27] for SDT, Prochaska and DiClemente [37] for TTM and Drieschner et al.[38] for IM. Priority was given to readily available Dutch versions of measurement instruments, but in case these were not available we chose to apply a translation procedure to the original English versions. Since our motivation feedback intervention is based on SDT, the primary outcome analysis is focused on this theory. Subsequently we will investigate how well the other two theories explain the effects of the intervention. Table 1 gives an overview of the instruments – questionnaires and interviews – that will be applied at baseline, monthly (for the intervention condition only) and at 12 months follow-up to patients and clinicians. It is estimated that the total duration of the assessment for clinicians takes 25 minutes per measurement occasion, while for patients this is 70 minutes.

**Table 1 T1:** Instruments used at two research contacts and monthly

	**Patients**		
	**T0 (Baseline)**	**Monthly**	**T1 (12 months)**
TMS-f	x		x
URICA-D	x		x
SoC Algorithm	x		x
PCS			x
TEQ	x		x
HCCQ	x		x
IS	x		x
Zoo Map test	x		x
HAQ	x		x
TCI	x		
MMAS	x		x
Stigma Scale	x		x
HoNOS*	x		x
BPRS*	x		x
MANSA*	x		x
SDT graph**		x	
	**Therapists**		
TMS-f	x		x
URICA-D	x		x
SoC Algorithm	x		x
HAQ	x		x
SES	x		x
SDT graph**		x	
Therapist motivation***		x	

* These measures are part of ROM as standard clinical practice, and are thus of no additional burden to the patient.

** Only patients and therapists in the motivation feedback condition fill in the SDT graph.

*** Only therapists in the motivation feedback condition fill in two items regarding their motivation to treat the patient.

**TMS-f:** Treatment Motivation Scale for forensic patients, **URICA-D:** University of Rhode Island Change Assessment – Dutch version, **SoC algorithm:** Stages of Change algorithm, **PCS:** Processes of Change Scale, **TEQ:** Treatment Entry Questionnaire, **HCCQ:** Health Care Climate Questionnaire, **IS:** Insight Scale, **HAQ:** Helping Alliance Questionnaire, **TCI:** Temperament and Character Inventory, **MMAS:** Morisky Medication Adherence Scale, **HoNOS:** Health of the Nations Outcome Scale, **BPRS:** Brief Psychiatric Rating Scale, **MANSA:** Manchester Short Assessment of Quality of Life, **SDT graph:** Self-Determination graph, **SES:** Service Engagement Scale.

### Primary and secondary outcomes

The primary outcome in this study is actual treatment engagement, as measured with the Service Engagement Scale (see paragraph on treatment engagement). Secondary outcomes in this study are treatment motivation, as measured with the Treatment Entry Questionnaire (see paragraph on SDT instruments), administrative data on missed appointments (see paragraph on treatment engagement), psychosocial functioning and quality of life (see paragraph on secondary outcomes).

#### Treatment engagement

Treatment engagement will be measured with the Service Engagement Scale (SES) that was constructed by Tait, Birchwood & Trower [39]. The SES has 14 items that are rated on a 4-point scale ranging from 0 (not at all) to 3 (most of the time). The four subscales refer to availability, collaboration, help seeking and treatment engagement. The scale will be administered to clinicians. The original English version of the SES has shown good psychometric properties [39]. As a more objective measure of treatment engagement, data from the patients’ files will be collected on the frequency of missed appointments with the main clinician, percentage of missed appointments over all appointments in the past year, reasons for discontinuation of care or drop-out (if applicable) and the number of admissions in the past year (voluntary and involuntary).

Furthermore, the Morisky Medication Adherence Scale (MMAS) [40] will be administered to only to patients with psychotic disorders to measure the level of antipsychotic medication adherence. The MMAS is a self-report scale that consists of 8 items asking about a specific medication-taking behaviour. The total scale score can range from 0 to 8, which will be discretized into high adherence (score of 8), medium adherence (score of 6 or 7) or low adherence (score below 6) [40]. The scale was found reliable (Cronbach’s α= 0.83) as a measure for blood pressure medication adherence in patients with hypertension [40] and has been adjusted to fit our study population of psychotic patients. Additionally, the psychiatrists of the patients with psychotic disorders will be asked every six months to indicate whether they believe the patient adheres to the antipsychotic medication and if not, to give reasons for the patient’s nonadherence.

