### Hypotheses

It is hypothesized that motivation feedback to clinicians on the treatment motivation of their patients will lead to an increase in both the quantity and quality of treatment motivation and treatment engagement of these patients. The patient’s self-reported motivation and the clinician-reported motivation of the patient are expected to induce more awareness regarding motivational issues that are at play during treatment, and subsequently to more suitable (motivational) interventions leading to better outcomes (i.e. treatment engagement and psychosocial functioning). More specifically, we expect the increase in quantity and quality of motivation will follow the patterns shown in Figure 1. For example, in the intervention group we expect a larger increase in autonomous motivation (concept from SDT), a larger proportion of patients making forward shifts in the stages of change (concept from TTM) and a larger increase in motivation to engage in treatment (concept from IM) relative to the control group. As a consequence, we expect the intervention group to show a higher level of treatment engagement than the control group at the time of follow-up, as demonstrated by higher clinician-rated treatment engagement, less no-shows and better antipsychotic medication adherence in the patients with psychotic disorders.

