### Statistical analyses

The data of the RCT will be analyzed according to the intention-to-treat principle. Baseline comparability between the intervention group and control group in demographic and clinical variables will be evaluated with independent samples t-tests and chi-square tests. Furthermore, non-responders (i.e. eligible patients who chose not to participate in the study) will be compared to responders with respect to background demographic and clinical variables with independent samples t-tests and chi-square tests. Logistic regression analysis will be applied to test for differences between the motivation feedback and control group with respect to the primary and secondary outcomes that are dichotomous variables, while (multiple) linear regression analysis will be used in case of continuous outcome variables. For individual categorical outcome variables, the effectiveness will be determined by odds ratios, including p-values (two-tailed). The effectiveness of the variables combined will be determined by ROC-curves (for categorical outcomes) and the individual odds ratios, R2 and the individual regression coefficients (for continuous outcomes). The Hosmer and Lemeshow goodness-of-fit test will be used in case of logistic regression. In case of multiple regression analysis the classical regression diagnostics will be applied for normality, (non)linearity, heteroscedasticity, (influential) outliers and interaction. A subgroup analysis will be performed for patients with psychotic disorders for the effects of the intervention upon their antipsychotic medication adherence. The analyses will be performed both unadjusted and adjusted for baseline differences of the distributions between the two treatment groups. In analyzing a specific outcome variable, the baseline score of that variable will be used as covariate. The analysis will be extended using multilevel analyses that takes the nesting of measurements into account. A clustering of outcomes is likely since a single clinician may treat several patients, and clinicians are clustered into teams. Multilevel modelling will be performed to check for any clustering effects on the primary outcome. In the multilevel analyses we consider the two measurements as the first level and the patient as the second level. We will explore whether the different treatment locations (FACT teams) and institutions (MHC Breburg and MHC WNB) can be considered as random factors in the modeling. We will identify predictive factors in estimating the outcome and whether there are predictive factors dependent on the type of treatment condition (interaction between baseline variables and treatment effect). Furthermore, we will take into account to what extent patients were exposed to the intervention by analyzing the dose-effect relationship. We expect (as is the case in most empirical studies in a psychiatric setting) that missing data will occur. We expect that the data will be Missing At Random (MAR), which is allowed to be a function of the observed variables (both covariates and outcome variables). If the assumption of MAR is violated, the pattern mixture model approach will be applied. In case predictor variables are missing, the method of multiple imputations or the maximum likelihood estimation method will be applied.

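### Cutting the 0-8 medication adherence score into three classes discards information in a supportive analysis limited to patients with psychotic disorders

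*Protocol article*

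**What the plan says.** The section on treatment engagement says the MMAS "will be administered to only to patients with psychotic disorders to measure the level of antipsychotic medication adherence". Totals lie between 0 and 8, and the article's plan for the total reads: "which will be discretized into high adherence (score of 8), medium adherence (score of 6 or 7) or low adherence (score below 6". The cut-offs carry a citation to the scale's source. Nowhere does the article say that the 0-8 total will itself be analysed.

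The Hypotheses section expects higher engagement in the intervention arm to show itself in three ways, one of them being "better antipsychotic medication adherence in the patients with psychotic disorders". The list under Primary and secondary outcomes does not contain the MMAS: it names the SES as primary, and the Treatment Entry Questionnaire, missed appointments, psychosocial functioning and quality of life as secondary.

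Under Statistical analyses, logistic regression is assigned to comparisons "with respect to the primary and secondary outcomes that are dichotomous variables". Continuous outcomes go to linear regression. For outcomes in classes the text adds: "For individual categorical outcome variables, the effectiveness will be determined by odds ratios, including p-values (two-tailed". Adherence among patients with psychotic disorders is described there as a subgroup analysis, and each outcome's own baseline score is to serve as covariate.

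**The concern.** The scale has nine ordered values, and the stated form keeps three. All scores from 0 to 5 become one value, and 6 and 7 become another. A patient who moves from 1 to 5 counts as unchanged, while one who moves from 5 to 6 counts as improved. Any analysis of the classes ignores the first kind of change.

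This matters more than it would for an outcome measured in everyone. The sample of 350 was sized for the SES across both diagnostic groups. The MMAS is answered only by the psychotic-disorder part, and the article gives no number or share for that part. At stake is the precision of one of the three results by which the hypotheses expect engagement to be demonstrated. The primary comparison is not at stake.

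**Working it through.** The article states no sample size or power for the MMAS, so there is no planned figure to reproduce. The check compares power with the score kept and with the score grouped.

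**Inputs from the protocol**
- Score range 0-8, with classes 8, 6-7 and below 6 (Treatment engagement).
- Two-sided alpha 0.05, cluster size 6, within-cluster correlation 0.07, total 350 (Sample size and power calculations).
- Allocation 1:1 (Procedures and randomization).

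**Assumptions, because the protocol gives no figure**
- Shift of 0.40 SD on a latent scale. This is the protocol's expectation for the SES, borrowed for the MMAS.
- 120, 174 or 230 patients with psychotic disorders, that is 120/350 = 34%, 174/350 = 50% or 230/350 = 66% of the sample.
- Control scores drawn from a normal variable, rounded and truncated to 0-8, with mean and SD chosen to span mostly low to mostly high adherence.

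**Method.** Draw n = N/2 scores per arm, with the intervention mean equal to the control mean + 0.40 × SD. Test the 0-8 score with a two-sided Wilcoxon rank test, then recode to three classes and repeat the same test. Without covariates, the rank test is the score test of the proportional-odds model, so both columns represent ordinal logistic analyses and differ only in the grouping. Power is the share of p-values below 0.05.

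**Results at N = 174** (6,000 runs per row; simulation error about √(0.7 × 0.3/6,000) = 0.6 points per entry)

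| Latent mean, SD | Control low/medium/high | Power, 0-8 score | Power, three classes | Loss |
|---|---|---|---|---|
| 4.5, 2.2 | 68/24/9% | 72% | 60% | 12 points |
| 5.5, 2.2 | 50/32/18% | 71% | 65% | 7 points |
| 6.0, 2.0 | 40/37/23% | 69% | 65% | 4 points |
| 6.5, 2.0 | 31/38/31% | 67% | 65% | 3 points |
| 7.0, 2.0 | 23/37/40% | 65% | 63% | 2 points |

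Losses are taken before rounding. With N = 120 and 230 they are of the same size, and with a majority of controls scoring 8 the loss falls to about 1 point. Across all the runs made for this check, the loss is about 1 to 13 points. It is largest when many patients fall below 6, because the grouping then merges most of the variation.

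**Clustering.** The protocol's inflation factor is 1 + (6 − 1) × 0.07 = 1.35. With 88 patients per arm (about a quarter of 350), the effective number is 88/1.35 = 65. A t-test on the score then has 59% power against 47% for the three-class rank test in the 68/24/9% mix, and 54% against 52% in the 23/37/40% mix. Absolute power falls, but the pattern of loss is the same.

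**Choice of model for the score.** Under a strong ceiling, a t-test on the score can fall slightly below the three-class ordinal test (63% against 64% at N = 174). The rank test on the score did not fall below it in any scenario. This favours an ordinal model over linear regression for the score.

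**The case against.** The strongest reply is that the plan already covers three-class outcomes. A reader who sees only "outcomes that are dichotomous variables, while (multiple) linear regression analysis will be used in case of continuous outcome variables" might infer that the three classes fit no planned model, that they must be merged into two so that logistic regression can be used, and that the open cut-point then invites selection and costs much more power. The documents do not support that chain. The odds-ratio provision for categorical outcomes shows that such outcomes were foreseen. A proportional-odds or multinomial logistic model reports odds ratios, and which variant is used can properly be left to an analysis plan that is not shown. Nothing says the classes will be merged, and both cut-points are fixed in advance. Nor does the article say that the baseline will enter as three classes; it speaks of the baseline score.

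It is also fair to say that the classes are the instrument's published ones and easy to interpret, that the analysis is supportive with no power claimed for it, and that the loss may be only 1 or 2 points if many patients score high.

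All of this stands, and it limits the point to efficiency. It does not remove the point: the article commits to discretising the total and states no analysis of the score, and published cut-offs are a reason to report the classes rather than to analyse only them.

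**Conclusion.** The point holds as a minor improvement. The only stated form of the adherence outcome discards information that the trial will already have collected. Even with a well-chosen three-class ordinal model, power is about 1 to 13 percentage points lower than with an ordinal model on the full score.

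That range rests on a borrowed 0.40 SD shift, assumed score distributions and an assumed 120 to 230 patients with psychotic disorders, without clustering or baseline adjustment. Only the direction of the loss is secure; its size depends on how adherent the patients are. It should not be read as an inconsistency between outcome and model, nor as a threat to the primary SES comparison or the listed secondary outcomes.

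**What to change.** State in the statistical section that the 12-month MMAS total (0-8) will be analysed with a proportional-odds (ordinal logistic) model, with the baseline 0-8 score as covariate and allowance for the randomised unit (team or clinician), for example as a random effect. Report the percentages in the three published classes by arm descriptively. Name this one model in advance, rather than choosing between linear and ordinal after seeing how many patients score 8.

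The cost is a sentence or two, with no new data. A common odds ratio on the score is less familiar to clinicians than class percentages, which is why those should stay in the report. The model also assumes that the odds ratio is similar across the scale, and the class percentages give readers a rough view of whether it is.

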#### SDT instruments

The types of motivation that are distinguished by SDT will be measured with the Treatment Entry Questionnaire (TEQ) [10,41]. It was shown that the TEQ was reliable (i.e. internally consistent) for external (Cronbach’s α = .89), introjected (Cronbach’s α = .89) and identified motivation (Cronbach’s α = .85) [41]. To our knowledge, the TEQ has not been studied in a Dutch population before. Therefore, we translated the original TEQ by Wild et al. [41] and adapted the wording to fit a population of patients with severe mental illness in psychiatric treatment (e.g. words that referred specifically to addiction treatment were replaced by words that reflected more general treatment by a mental health center). Two translators performed independent forward translations of the original TEQ into Dutch and adapted the wording to fit its application to outpatient psychiatric treatment. A consensus version was established, consisting of 27 items that can be rated on a 7-point Likert-scale ranging from 1 (strongly disagree) to 7 (strongly agree). The psychometric properties of this Dutch TEQ are to be investigated in this study.

The Health Care Climate Questionnaire (HCCQ) will be used to measure the degree to which clinicians are perceived to be autonomy supportive. Items are scored on a Likert scale, ranging from 1 (strongly disagree) to 7 (strongly agree). The HCCQ has 15 items that have been used in studies of weight loss [42] (Cronbach’s α =.92) and smoking cessation [43] (Cronbach’s α = .96). Application of a Dutch HCCQ is not known to us. Therefore, the original HCCQ was translated into Dutch by two independent translators who subsequently established a consensus version. This consensus version was back translated into English by two independent expert translators to check for discrepancies between the original version and the backtranslation. On the basis of consensus between all translators, the final Dutch questionnaire was achieved. The psychometric properties of the Dutch HCCQ will be determined in this study.

#### TTM instruments

The stages of change will be measured by staging algorithms and the University of Rhode Island Change Assessment – Dutch version (URICA-D). Algorithms are capable of placing individuals in one of five stages and have been used extensively in diverse populations and research areas [37,44,45]. The algorithm approach involves several questions that ask about attempts and intentions to change behaviour within certain time frames corresponding to a particular stage. Both patients and clinicians will be asked to judge whether the patient is currently in the precontemplation, contemplation, preparation, action or maintenance stage with regard to the patients’ motivation to change his psychiatric problems and specific problem behaviours if relevant (e.g. alcohol abuse, drug abuse and criminal behaviours). Precontemplation is defined as ‘not planning to work on my problems in the next six months’. Contemplation is defined as ‘planning to work on my problems within the next six months, but not within 30 days from now’. Preparation is defined as ‘planning to work actively on my problems within the next 30 days’. Action is defined as ‘having worked on my problems actively for the last 30 days, but no longer than six months’. Maintenance is defined as ‘having worked actively on my problems for the last six months’. These definitions are similar to other stage algorithms from TTM [46].

The URICA-D is the Dutch version of the URICA [47], which is a self-report scale that asks the patient to first enter a problem and then to indicate on a five point Likert scale (1 = strongly disagree to 5 = strongly agree) how much he agrees with a particular statement. The URICA-D consists of four subscales which represent four stages of change: precontemplation, contemplation, action and maintenance. The reliabilities (i.e. Cronbach’s alpha) for the subscales have been found to range from 0.84 to 0.95 [48].

The processes of change will be measured by asking patients to indicate how often they make use of the strategies described in 20 statements, where each process of change is represented by two statements. The statements are rated on a five point Likert scale, ranging from 1 (never) to 5 (repeatedly), consistent with other measures of the processes of change in TTM [49-51]. Application of the processes of change scale in a Dutch psychiatric patient population is not known to us. Therefore, we developed a questionnaire based on the original English questionnaire by Prochaska et al. [50] and adapted it to a population of people with mental illness in psychiatric treatment. Two translators performed independent forward translations of the Processes of Change Scale (PCS) [50] into Dutch and adapted the wording to fit its application to change processes in psychiatric treatment. From the 40 items generated in this translation procedure, a consensus version was established from which 20 items were chosen (two items per process) as most relevant to create a short form of the processes of change inventory, consistent with other short forms of the processes of change inventory (e.g. in the studies of [49,52]). The psychometric properties of our scale are to be investigated in this study.

The decisional balance constructs and self-efficacy constructs are incorporated in the Treatment Motivation Scale for forensic patients [38], a scale that will be used to measure the constructs of the IM (see next section).

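### The printed stage-of-change definitions are neither exhaustive nor exclusive: patients who began active work less than 30 days ago are likely to be rated one stage off

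*Protocol article*

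**What the plan says.** The TTM instruments section states that "Algorithms are capable of placing individuals in one of five stages". Patients and clinicians are each asked to judge which of the five stages the patient is in, for psychiatric problems and, where relevant, for specific behaviours such as alcohol or drug abuse.

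Two of the printed definitions rest on past work. The final stage reads: "Maintenance is defined as ‘having worked actively on my problems for the last six months". The stage that comes just before it has both a lower and an upper limit: "Action is defined as ‘having worked on my problems actively for the last 30 days, but no longer than six months".

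The other three rest on intention. The one nearest to a start reads: "Preparation is defined as ‘planning to work actively on my problems within the next 30 days". Contemplation is a plan to begin later than a month from now but inside half a year, and Precontemplation is the absence of any plan over that half-year.

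Under Hypotheses, one of the expected effects in the intervention group is "a larger proportion of patients making forward shifts in the stages of change (concept from TTM". Table 1 lists the algorithm for patients and for therapists at T0 and T1 only, in line with the Design and setting section: "There will be two extensive measurement occasions for both groups: at baseline and follow-up at 12 months".

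**The concern.** The first three stages look forward (when will work start?) and the last two look back (how long has work gone on?). The two scales do not meet at the present day. Preparation ends at a start that is still to come, while Action begins only after 30 days of work. A patient two weeks into active work is past the one and short of the other.

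The join matters because moving from Preparation to Action is the step from intending to doing, and the trial predicts more forward steps in the feedback group. A patient who takes that step shortly before the 12-month visit may not be counted as having reached Action. A patient who had just taken it at baseline may be recorded one stage too low at the start. With two ratings a year apart, no intermediate rating can recover either patient. The same category also feeds the TTM side of the theory comparison.

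**Working it through.** The article states no figure on this point, so this is a check of the definitions. Let *d* be the number of days since active work began, from 0 to 365 (366 values). Six months is taken as 180 days, which is an assumption.

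**People not yet working.** A planned start in 1 or 30 days gives Preparation. A start in 31 or 180 days gives Contemplation. A start in 181 days, or none, gives Precontemplation. These three stages adjoin without gap or overlap.

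**People already working.** Two phrases can each be read in two ways: the 30-day phrase in Action (a duration, or any time in that period) and Preparation (only people who have not started, or anyone who plans to work in the next 30 days, including those who plan to continue).

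| Preparation | 30-day phrase in Action | Days with no stage | Days with one stage | Days with more than one stage |
|---|---|---|---|---|
| Not yet started | Duration | 0–29 (30 days) | 30–179 Action (150); 181–365 Maintenance (185) | 180 (1 day) |
| Anyone planning to work | Duration | none | 0–29 Preparation (30) | 30–365 (336 days) |
| Not yet started | Any time in the period | none | 0–179 Action (180); 181–365 Maintenance (185) | 180 (1 day) |
| Anyone planning to work | Any time in the period | none | none | 0–365 (366 days) |

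The first row adds up: 30 + 150 + 185 + 1 = 366.

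**Which reading fits the text.** Only the third row is clean apart from day 180. It needs the 30-day phrase to mean *at some time in the last 30 days*. That conflicts with the rest of the Action definition, whose upper limit of six months is a limit on duration. It also conflicts with Maintenance, whose parallel phrase must be a duration if it is to differ from Action. So the first two rows are the plausible ones. In the first, recent starters match nothing. In the second, they are placed in Preparation although they have begun, and everyone further along who means to continue also qualifies for Preparation.

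**After the rewording given under the fix.** Action covers days 0–180 (181 days) and Maintenance covers days 181–365 (185 days): 181 + 185 = 366. Preparation is closed to people already working. No day is left without a stage, and none between Preparation, Action and Maintenance is counted twice.

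**The case against.** The strongest reply is that the instrument is not shown. The article says the algorithm consists of several questions about attempts and intentions, and it prints only one-line definitions. Insufficient Dutch is an exclusion criterion, so the forms are presumably in Dutch and the English is a rendering. A point that turns on one preposition may disappear on the form itself. This stands as a limit on certainty. It does not make the printed definitions consistent, and if the form resolves the point, the printed text should say so.

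Four stronger readings are tempting, and the documents do not support them.

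- *Recent starters have no stage and become missing data.* Raters choose among five named stages, and Preparation is not expressly limited to people who have not begun. A neighbouring stage is the likely outcome.
- *About 1 in 6 recent movers is affected (30/180 days).* This assumes starts spread evenly over six months and applies only to patients who began in that period. The article gives neither the spread nor that share. The share may be modest: patients are already in outpatient treatment, and the Study population section notes that most definitions of severe mental illness include at least two years of treatment or illness.
- *The URICA-D cannot help.* It has no preparation subscale, so it cannot rebuild the five-stage category. It does have an action subscale, the article describes no time windows for it, and Table 1 lists it for patients and therapists at both visits. It is a partial second measure at this boundary.
- *The trial's main result is at risk.* The primary outcome is the SES and the listed secondary motivation measure is the TEQ. Stage shifts are one of three examples of expected motivational change, and the theory comparison is exploratory.

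**Conclusion.** The point holds for the definitions as printed. They do not join between Preparation and Action, and they overlap at exactly six months. The overlap is a single point and trivial; the 30-day stretch is what matters.

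The probable consequence is misclassification by one adjacent stage, most likely into Preparation, for patients who began active work less than 30 days before a rating. Patient and clinician may resolve the ambiguity differently. This adds some error to the forward-shift hypothesis and to the exploratory TTM modelling. It does not touch the primary outcome or the TEQ. The documents give no basis for a size. The wording is the same in both arms, and I make no claim about the direction of any effect on the group comparison.

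The conclusion assumes that the 30-day phrase is a duration and that the questionnaire follows the printed definitions. The weight is minor, but a named hypothesis uses the measure and the correction is cheap.

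**What to change.** Use the same three wordings in the patient and clinician versions:

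- Preparation: *not yet working actively on my problems, but planning to start within the next 30 days*.
- Action: *started working actively on my problems within the last six months*.
- Maintenance: *working actively on my problems for more than six months*.

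All three changes are needed. If Preparation is left as it is, anyone already working who plans to go on still fits both it and Action or Maintenance. Precontemplation and Contemplation can stay unchanged, on the understanding that they describe people who are not working on their problems now.

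If the questionnaire already separates these groups, leave it alone and correct the printed definitions to match. The change adds no items, respondent time or analysis. The price is slightly less literal agreement with the source algorithm's wording.
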